#### Statistical analysis plan

##### Primary efficacy analysis

The estimate of the proportion of cases demonstrating OPM (OPM positive) and the associated 95% CI will use standard statistical methods. The CI will be based on the Clopper-Pearson exact approach.

##### Secondary efficacy analyses

The estimate of the proportions of OPM demonstrated/not demonstrated and LAT complete/LAT incomplete and the associated 95% CIs will use standard statistical methods. The CI will be based on the Clopper-Pearson exact approach. The comparison of the RFS and OS between OPM positive and OPM negative patients will be illustrated with Kaplan-Meier curves; the HR will be estimated using Cox regression. AE data and the impact on oncological treatment plans will be summarised in tables and listings.

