## Introduction

Lung cancer is the most common cause of cancer-related death. Despite major advances in staging and potentially curative treatments (surgery and radiotherapy (RT)), recurrence rates remain unacceptably high. In patients with stages I, II and IIIA, non-small cell lung cancer (NSCLC) 2-year mortality is currently 15%, 30%^1^ and 50%,^2^ respectively. A likely reason for this is radiologically occult metastatic disease and novel staging tools are urgently required. Recent studies have highlighted minimal pleural effusion (mini-PE) as a marker of particularly high recurrence risk, and excess mortality following radical treatment.^3 4^

Mini-PE has been defined as a small pleural collection ipsilateral to the primary tumour, which is either too small to safely aspirate for a cytology sample, or one that has been aspirated and initial fluid cytology is negative (see figure 1). Mini-PE affects up to 25% of patients presenting with NSCLC,^3^ although half of these occur in patients with metastatic disease.^3 4^ Since 2014, two large retrospective series have described clear association between excess mortality following radical treatment for stages I–IIIA NSCLC and mini-PE on diagnostic (pretreatment) CT imaging. These series conclude that mini-PE reflects occult pleural metastases (OPM) in up to 80% of patients.^3 4^ However, this is based on indirect evidence and supportive follow-up imaging. In both series, it is acknowledged that other factors may have contributed to the adverse survival observed, including benign pleuritis, systemic comorbidities^5 6^ and undertreatment due to the suspicion of OPM.

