#### Survival

Overall survival (OS) will be recorded from date of registration until death from any cause. Participants alive at 6 months will be censored. Recurrence-free survival (RFS) will be recorded from treatment completion date to disease recurrence or death from any cause.

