### Statistical considerations

#### Sample size

The target sample size of 50 patients will allow estimation of the prevalence of OPM, AE rate and the impact on treatment plans with 95% CI bounds not exceeding 10% if the OPM prevalence is ≤15%. This represents a change in estimated prevalence, which was initially set at 70% (requiring a minimum sample size of 96). The initial OPM estimate of 70% reflected solely the retrospective data previously reported.^3 4^ The updated estimate of OPM prevalence and sample size calculation acknowledges data from the first 12 recruits to STRATIFY, of whom only one case of OPM has been observed (8.3% OPM rate).^19^ The reduction in the sample size from 96 to 50 cases means the trial will no longer have adequate power (80%) to detect an OS HR of 0.5 as planned in previous iterations of this protocol. This original HR corresponded to data from previous retrospective studies, which reported a median OS in OPM positive 6.32 months vs 12.65 months in OPM negative cases.^4^ OS differences between OPM positive and OPM negative groups will nevertheless be reported. Post hoc power calculations taking account of the observed prevalence will be performed.

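### With about 4 OPM-positive patients and about 2 deaths among them expected by 6 months, the planned Cox hazard ratio has no finite value in roughly one trial in eight and needs a sparse-event method

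*Protocol article*

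**What the plan says.** Under Secondary efficacy analyses, the comparison of recurrence-free survival (RFS) and OS between OPM-positive and OPM-negative patients "will be illustrated with Kaplan-Meier curves; the HR will be estimated using Cox regression". Under Survival, the OS window is short: "Participants alive at 6 months will be censored".

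The Sample size section supplies the other inputs. "The target sample size of 50 patients will allow estimation of the prevalence of OPM" (among other quantities) "with 95% CI bounds not exceeding 10% if the OPM prevalence is ≤15" per cent. The prevalence assumption, "which was initially set at 70% (requiring a minimum sample size of 96"), was revised after the first 12 recruits, "of whom only one case of OPM has been observed (8.3% OPM rate"). The section gives retrospective median OS of 6.32 months for OPM-positive and 12.65 months for OPM-negative cases. It accepts that "the trial will no longer have adequate power (80%) to detect an OS HR of 0.5", says that OS differences will still be reported, and promises post hoc power calculations.

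The Introduction gives a second, milder picture of survival for stage I to IIIA disease in general: "non-small cell lung cancer (NSCLC) 2-year mortality is currently 15%, 30" and 50 per cent for stages I, II and IIIA respectively.

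**The concern.** Cutting the sample and the expected prevalence together shrinks the OPM-positive group from about 67 patients (70% of 96) to about 4 (8.3% of 50), and only deaths in the first 6 months count. A Cox model with one binary covariate needs at least one death in each group while both groups are at risk. Without an OPM-positive death the likelihood keeps rising as the HR falls towards 0. Software then prints a meaningless value with a huge standard error, or a warning.

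This differs from low power, which gives a wide but valid interval. Here the numerical summary may not exist, and post hoc power calculations do not help. If the fallback is chosen only after seeing no deaths, the choice depends on the data.

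**Working it through.** **Inputs.** N = 50; prevalence 1/12 = 8.3%, with 15% as the upper planning value; medians 6.32 and 12.65 months (all from Sample size); censoring at 6 months (Survival); 2-year mortality 15%, 30% and 50% (Introduction). Exponential survival and independent OPM status are assumptions.

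**1. The plan's own figure.** Normal-approximation sample size for a 10-point half-width at 15%: n = 1.96² × 0.15 × 0.85 / 0.10² = 48.98, so 49. With N = 50 the half-width is 1.96 × √(0.15 × 0.85 / 50) = 0.099. The stated 50 is reproduced. It was chosen for prevalence, not for survival.

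**2. Expected numbers.**
- OPM-positive patients: 50/12 = 4.2. OPM-negative: 45.8.
- Probability of death by 6 months, OPM-positive: 1 − exp(−6 ln2 / 6.32) = 0.482, so 4.2 × 0.482 ≈ 2.0 deaths.
- OPM-negative: 1 − exp(−6 ln2 / 12.65) = 0.280, so 45.8 × 0.280 ≈ 12.8 deaths.

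**3. Chance of no finite HR on the plan's medians.** P(no OPM-positive death) = (1 − prevalence × 0.482)^50.
- 8.3%: 0.129. This includes (11/12)^50 = 0.013 with no OPM-positive patient at all.
- 15%: 0.023.
- 5%: about 0.30. 10%: about 0.085.

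Simulation agrees: about 13% at 8.3% and about 2% at 15%. At 8.3%, P(0 or 1 OPM-positive death) ≈ 0.40.

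**4. Precision when the HR exists.** SE(log HR) ≈ √(1/2.0 + 1/12.8) = 0.76, so the 95% CI spans a factor of about exp(1.96 × 0.76) = 4.4 either side.

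**5. Sensitivity to better survival (8.3% prevalence).** A 12.65-month median implies 2-year mortality of 1 − exp(−24 ln2 / 12.65) = 73%, above all three Introduction figures. OPM-negative patients may therefore live longer than the retrospective median suggests.

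| OPM-negative 2-year mortality | No finite HR, OPM-positive median 6.32 months | No finite HR, OPM-positive hazard only doubled | OPM-positive median implied by doubling |
|---|---|---|---|
| 15% | 28% | 77% | 51 months |
| 30% | 16% | 52% | 23 months |
| 50% | 14% | 29% | 12 months |

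In the first result column the floor is the 12.9% from step 3. The excess comes from the opposite failure, where no informative OPM-negative death occurs.

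**6. The alternative estimator.** On the plan's medians at 8.3% (true HR 12.65/6.32 = 2.0), the median standard Cox HR among trials that yield one is 2.2 to 2.3, and the median Firth HR is 2.4. Firth gives a value in about 99% of trials there. Across the scenarios with doubled hazard and with the plan's medians, its profile-likelihood interval covers the true HR in about 94% to 98% of trials that yield one.

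**7. Exact proportions.** These remain reportable with no deaths: 4 of 4 alive gives a Clopper-Pearson lower limit of 0.025^(1/4) = 0.40, so 40% to 100%.

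**The case against.** The strongest reply is that the problem is modest, mostly disclosed and possibly handled elsewhere. On the plan's medians seven trials in eight do yield an HR. The article says openly that the OS comparison has lost its power, and no decision rests on this HR. A rule for sparse events could sit in an analysis plan that is not shown, and the words used do not exclude a penalised Cox fit. Much of this stands and limits the weight of the point. What remains is that the article names the method and commits to reporting the comparison, and that its concession concerns power, not existence of the estimate.

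Three stronger readings are tempting, and the documents do not support them.

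- **That the HR will usually be inestimable.** The 29% to 77% figures need an OPM-positive hazard merely double that of stage I to IIIA patients in general. This implies OPM-positive medians of 12 to 51 months, against the only value given, 6.32 months.
- **That a reported HR would seriously overstate the effect.** On the plan's medians the upward shift is small, and Firth does not remove it.
- **That nothing else would be reported.** Kaplan-Meier curves are planned too and can be drawn even if no OPM-positive patient dies. In that case a likelihood-based interval from ordinary Cox still has a finite upper limit.

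The 6-month window matters as well. At 8.3% prevalence and the plan's medians, the share with no finite HR would be 4% to 5% at 12 months and about 2% at 24 months.

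**Conclusion.** The point holds in a limited form. On the article's own figures the standard Cox HR for OS has no finite value in about 13% of trials at 8.3% prevalence and about 2% at 15%. At 8.3%, about 40% of trials have no more than one OPM-positive death to estimate it from. If OPM-negative patients do as well as the Introduction's figures and OPM-positive patients keep the 6.32-month median, the share is about 14% to 28%.

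These figures assume exponential survival and complete 6-month follow-up. They also depend on a prevalence known from only 12 patients (exact 95% CI 0.2% to 38.5%), so the true share could be clearly lower or higher. RFS was not calculated, but the same small OPM-positive group applies. The primary endpoint is unaffected. This is a worthwhile, low-cost correction to a secondary analysis.

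**What to change.** In Secondary efficacy analyses, state that:

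- the lead OS result is the number and proportion alive at 6 months in each OPM group, with Clopper-Pearson 95% CIs (the interval method the article already uses), alongside the Kaplan-Meier curves;
- the HR comes from Firth-penalised Cox regression with a profile-likelihood 95% CI and is labelled descriptive, with the same method for RFS where an HR is given.

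Settle this before OS is examined by OPM status. If the full analysis plan already has such a rule, a reference to it is enough.

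The cost is one sentence and standard software, with no new patients or data. The proportions need complete 6-month vital status, and there is none for a group with no patients. With very few events the penalised HR leans on the penalty and keeps its small-sample bias. It is still unavailable if there are no OPM-positive patients or no deaths.

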##### Exploratory analyses

The number of recruits with banked samples suitable for later analysis will be reported but no other analysis will be performed under this protocol.

##### Safety analysis

AE data will be summarised in tables and listings.

### Changes to protocol

The protocol described here reflects the current version 5.0, dated 16 November 2022. The following changes were made in previous versions:

#### V.2.0, dated 26 June 2020

The definition of the primary endpoint (OPM) was clarified to make it clearer that pleural fluid samples could be sent for routine cytology assessment, alongside parietal pleural biopsies if these were taken

#### V.3.0, dated 25 February 2021

The maximum size used to define mini-PE in the inclusion criteria was changed from <40 mm maximum depth on axial CT images to an effusion occupying <1/3 of the hemithorax on erect chest radiograph. The original definition (drawn from previous retrospective mini-PE studies)^3 4^ proved difficult to deploy reliably in practice due to variation in where the user could make this measurement.Schedule of assessments updated to include a COVID swab prior to thoracoscopy (Visit 2), in line with COVID-19 guidance at that time.

At this point, a major protocol amendment was undertaken to address significant recruitment challenges, including (1) a change in the diagnostic pathway for lung cancer prompted by COVID-19, with a move to virtual consultations in many centres, (2) low lung cancer referral rates, which dropped by 60% in some networks and (3) significant delays in opening sites due to UK-wide prioritisation of Urgent Public Health-badged studies. One-to-one sessions with our current sites revealed a series of changes to patient flow and visit scheduling that would make the current protocol, which assumed as series of sequential face to face visits, undeliverable. These discussions also identified other recruitment barriers including the handling of tiny contralateral effusions (currently an exclusion criterion) and use of surgical thoracoscopy (under general anaesthetic) which has become more available in some centres since the original protocol design. Based on this feedback and following PPI review, v 4.0, dated 19 November 2022 was deployed implementing the following changes:

#### V.4.0, dated 16 November 2022

Introduction of remote verbal consent as an option, with subsequent written consent at next contact.Allowing completion of screening, consent, registration and baseline data collection on the day of thoracoscopy if this aligns better with local pathways and patient preference.Allowing recruitment earlier in the diagnostic pathway so that STRATIFY pleural staging can be completed without prior histological confirmation of NSCLC. This reduces the burden of invasive tests and necessarily broadens the eligibility criteria to ‘suspected or confirmed stages I–III lung cancer’.Allowing STRATIFY pleural staging to be performed by surgical thoracoscopy (ie, under general anaesthetic); this opens the study to centres without access to LAT.Allowing inclusion of cases with bilateral PEs, assuming the collection ipsilateral to the primary is judged to be suspicious, for example, asymmetrically large, with a small contralateral effusion.

A further, final protocol amendment was then made to ensure the study could report on the primary endpoint within its original funding envelope by extending the original recruitment period to 31 October 2023 via a no cost extension from the funder (CSO). This involved the following additional changes:

#### V.5.0, dated 16 November 2022

Removal of the MRI substudy, which involved perfusion MRI after registration and prior to thoracoscopy. Overall, 3/42 recruits had completed MRI by this time and these data will be reported in the results publication.Reduction of the sample size from 96 to 50. This was based on review of the OPM prevalence in the first 12 participants (see the Sample size section) and will allow the primary endpoint to be reported with the same precision as originally intended, but with a more realistic recruitment target.

### Definition of end of study

The end of study definition will be the date of last data capture, which will be met when all outstanding data has been returned from all sites, all required data queries have been resolved and the database is finalised for analysis.

### Monitoring, data management and quality assurance

No routine site or telephone monitoring will be performed. If issues arise, an on-site visit or telephone monitoring call will be arranged. The Cancer Research UK (CRUK) Clinical Trials Unit (CTU) will regularly chase outstanding data and queries. Routine requests for missing or queried data will occur quarterly.

### Safety considerations

All AEs and serious AE (SAEs) thought to be related to study procedures will be recorded. This includes AEs resulting from ultrasound, chest radiographs, venous blood sampling, LAT or VATS. Although the MRI substudy has been removed from the current protocol, any AEs or SAEs related to the MRI in the three patients recruited to the substudy prior this point will be reported. This will include any events related to image acquisition, including administration of gadolinium contrast, or the X-ray of orbits (if required) which were the only additional AEs recorded. Safety reporting is overseen by the Pharmacovigilance Department of the CRUK CTU Glasgow as delegated by the trial sponsor.

### Dissemination

Study results, including those related to the MRI substudy removed from the current protocol version, will be presented at national and international scientific meetings and published in full in a peer-reviewed journal.

### Study management

STRATIFY will be coordinated from the CRUK Glasgow CTU. The SMG, comprising the chief investigator, selected coinvestigators, project manager, statistician, trial coordinator, PV coordinator, PPI representative and IT programmer meet monthly to oversee the study.

## Data Availability

Data are available on reasonable request. Study results, including those related to the MRI substudy removed from the current protocol version, will be presented at national and international scientific meetings and published in full in a peer-reviewed journal.
